### Eligibility

*Inclusion criteria* are:

1. Aged 18 months to 14 years inclusive with recurrent PBB, CSLD or bronchiectasis.

2. Receipt of meningococcal C conjugate vaccine at least six months before enrolment;

3. Negative urine pregnancy test if post-menarchal female.

4. Provision of written informed consent from parent/guardian (assent if child aged ≥10 years).

5. Parent/child willing and able to meet the requirements of the protocol.

6. Access to a telephone and not planning to move from the study area in the 14 months post-enrolment.

7. Has experienced two or more respiratory exacerbations in the 18 months prior to study entry.

*Exclusion criteria* are: chronic lung conditions other than co-existent asthma and those under investigation in this study; prior vaccination with PHiD-CV vaccine; received the 23-valent pneumococcal polysaccharide vaccine (Pneumovax-23, Commonwealth Serum Laboratories Biotherapies, Melbourne, Victoria, Australia) within the previous two months; contraindication/known hypersensitivity to PHiD-CV and/or quadrivalent (ACYW_135_) meningococcal conjugate vaccine; immunosuppressive condition or immunodeficiency disorder that may influence responses to vaccines; systemic immunosuppressive therapy; administration of immunoglobulins and/or blood products within 90 days of receiving study vaccine; active participation in a clinical trial of another investigational drug/vaccine or therapy; acute illness at the time of enrolment, and other medical conditions that could increase the risk of serious adverse events (SAEs) from being in the study.

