### Randomisation, allocation and blinding

An independent biostatistician prepared the randomisation code using a permuted blocking design (block size of four) to maintain group balance. Randomisation was stratified by site, age (less than six years and six or more years), and PBB vs CSLD/bronchiectasis. The age of six years was chosen as at this age spirometry can be performed reliably in children. Treatment allocation is determined by the trial pharmacist at the Royal Children’s Hospital, Brisbane based on the randomisation list provided by the independent statistician. At the time of randomisation, the child’s study specific stratum is confirmed and a request for randomisation based on that stratum is provided to the pharmacist. The trial pharmacist selects the next consecutively numbered opaque sealed envelope from the relevant strata pack, opens the envelope and extracts the randomisation code. This is checked against the randomisation list and a vaccine pack matching the allocation code is assigned to the participant. The allocation sequence is concealed at all times throughout the study from all blinded investigators, study staff and participants.

Since the vaccines differ in colour, their preparation and delivery will be performed by nurses at each participating centre who are independent of the study. Unblinding of individual participants will only occur in emergency situations and ideally after discussion with the Data Safety Monitoring Committee (DSMC). The randomisation code will be unblinded once the database is locked and the data analysed.

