### Sample size

Prospective data collected in Brisbane children with non-CF bronchiectasis indicate a mean annual incidence of 2.1 (standard deviation 1.046) exacerbations requiring hospital clinic attendance or hospitalisation. PHiD-CV efficacy against exacerbations in children with bronchiectasis is unknown. However, based on the aforementioned pilot data and AOM data from the POET study (30% reduction) [33], our trial is powered to detect a 30% reduction from 2.1 to 1.47 exacerbations in the 12 months following the second vaccine dose. Assuming a Poisson distribution, 93 children per group will provide 90% power (α = 0.05, two-sided) to detect a 30% reduction in exacerbations in the PHiD-CV group and 80% power to detect a 25% reduction. Assuming a 10% loss to follow-up, we will recruit 206 children (103 per group). Differences of less than 20% are unlikely to change clinical practice without additional supporting evidence.

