### Analysis

Data will be presented in accordance with the updated CONSORT criteria [43]. Demographic data will be tabulated and expressed as proportions and/or means of the selected characteristics by vaccine group with the corresponding 95% confidence intervals. Differences between groups will be assessed by the normal test for comparisons of means and χ^2^ tests for comparison of proportions.

The primary analysis will assume a Poisson distribution and will compare the incidence of respiratory exacerbations between the two groups. Vaccine efficacy (VE) (%) will be calculated as (1 – Relative Risk (RR))*100 where RR represents the ratio of the incidence of exacerbations in the PHiD-CV group to the incidence in the control group (and presented with its 95% CI). All analyses will be performed on an intention-to-treat basis and will account for baseline stratification.

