#### Secondary analyses

The proportion of children with nasopharyngeal carriage of *H. influenzae* and *S. pneumoniae* at each time point will be compared between vaccine groups and presented as RR and 95% CI, adjusted for repeated measures. VE (%) against carriage will be calculated as (1-RR)*100 and presented with its 95% CI. Bacterial load at each time point will be compared.

Serum and mucosal antibody responses to *H. influenzae* proteins, including PD, pneumococcal protein and polysaccharide antigens and opsonophagocytic killing assays: geometric mean titres at each sampling time point will be compared between groups presented as a mean difference (and 95% CI) from linear regression models. In addition, the proportion of children assessed to be seropositive will be compared between groups at each sampling time point using χ^2^ tests for proportions and logistic regression models to adjust for stratification. All differences will be presented with their 95% CIs.

Safety and reactogenicity of vaccination: descriptive analyses will be performed on the number, type and severity of local and systemic reactions and SAEs that occur following vaccination and presented by treatment group. Comparisons between groups will be performed using Student’s *t*-test for continuous variables and χ^2^ tests for proportions.

Sub-group analyses will be performed for all primary and secondary objectives to examine potential differences by study specific strata. Univariate and multivariate analyses will be performed to evaluate variables independently associated with study endpoints and to assess potential confounding factors in the association between vaccination and disease.

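### Prior exacerbation count is not among the stated adjustments for the primary Poisson comparison; prespecifying it, with an overdispersion-robust variance, is a modest efficiency gain

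*Protocol article*

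**What the plan says.** All references are to the protocol article.

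- **Analysis**, primary comparison: "The primary analysis will assume a Poisson distribution and will compare the incidence of respiratory exacerbations between the two groups". Adjustment: "All analyses will be performed on an intention-to-treat basis and will account for baseline stratification". No other covariate is named.
- **Randomisation, allocation and blinding**: "Randomisation was stratified by site, age (less than six years and six or more years), and PBB vs CSLD/bronchiectasis". Exacerbation history is not a stratifier.
- **Eligibility**, inclusion criterion 7: "Has experienced two or more respiratory exacerbations in the 18 months prior to study entry". This documents a threshold. The article does not say whether the exact number is recorded; the section on intervention, follow-up and data collection mentions only a general medical history and respiratory status at baseline.
- **Analysis**, after the demographic table: "Differences between groups will be assessed by the normal test for comparisons of means", with chi-squared tests for proportions.
- **Secondary analyses**: univariate and multivariate models, in part "to assess potential confounding factors in the association between vaccination and disease". No variables are listed.
- **Sample size**: a pilot "mean annual incidence of 2.1 (standard deviation 1.046) exacerbations requiring hospital clinic attendance or hospitalisation", and "our trial is powered to detect a 30% reduction from 2.1 to 1.47 exacerbations in the 12 months following the second vaccine dose", with 93 children per group for 90% power.

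**The concern.** A child's recent exacerbation frequency is the nearest baseline counterpart of the primary outcome. Staff must assess it to apply criterion 7. If children differ in underlying risk, a model without it leaves explainable between-child variance in the comparison and gives up some precision. The recomputed power for a 30% reduction is about 89 to 90%, so there is little slack.

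The plan's other uses of baseline data do not fill this gap. Under concealed random allocation, a baseline difference between arms is chance, so a P-value for it does not inform the vaccine comparison. A search for confounders of a randomised effect has limited purpose. With no variable list and no statement that the primary estimate stands regardless, it also leaves room for more than one vaccine efficacy figure.

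**Working it through.** **1. The plan's own figure.** Inputs from the Sample size section: control rate 2.1, vaccine rate 1.47 (ratio 0.70), two-sided alpha 0.05, power 90%, 12 months of follow-up.

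- Rate difference: n = (1.960 + 1.282)² × (2.1 + 1.47) / 0.63² = 94.5 per group.
- Log rate ratio: n = (1.960 + 1.282)² × (1/2.1 + 1/1.47) / (ln 0.70)² = 10.507 × 1.1565 / 0.1272 = 95.5 per group.
- Square-root transform: 93.8 per group.

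At 93 per group, power is 0.892 to 0.898. The stated 93 is reproduced closely. On the log scale the SE is √(1.1565/93) = 0.112.

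**2. What the pilot SD shows.** Variance/mean = 1.046²/2.1 = 1.094/2.1 = 0.52. A Poisson count with mean 2.1 has SD √2.1 = 1.449. The pilot variance is below Poisson, so it shows no excess between-child variance for a covariate to explain.

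**3. Closed-form illustration if there is excess variance (dispersion φ assumed).** Power = Φ(0.3567/√(φ × 1.1565/93) − 1.96).

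- φ = 1: 89.2%
- φ = 1.5: 74.3%
- φ = 1.35 (10% less variance than 1.5): 78.6%

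**4. Simulation of the added covariate.** There were 93 children per arm and a true ratio of 0.70. Each child has a gamma frailty with mean 1 and variance k (assumed). Prior counts are Poisson over 18 months, entry requires two or more, and the control mean among entrants is held at 2.1. A Poisson regression on arm was compared with one on arm plus log prior count. Power uses the sandwich variance. The first figure in each cell is from 1,500 replicates, the second from a repeat with 6,000.

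| k | Variance ratio, adjusted/unadjusted | Power without count | Power with count |
|---|---|---|---|
| 0 (pure Poisson) | 1.00; 1.01 | 0.89; 0.90 | 0.89; 0.90 |
| 0.2 | 0.95; 0.96 | 0.82; 0.81 | 0.84; 0.84 |
| 0.4 | 0.90; 0.89 | 0.77; 0.77 | 0.82; 0.82 |
| 0.8 | 0.85; 0.82 | 0.72; 0.71 | 0.79; 0.80 |

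For k of 0.2 to 0.8 the variance falls by about 5 to 20% and power rises by about 2 to 9 points.

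**5. Why the variance estimator matters.** In the first run the model-based Poisson SE of the log rate ratio stayed at about 0.112 in every scenario, with or without the covariate. It does not register the heterogeneity, so it cannot register the gain. With no true effect (6,000 replicates), tests using that SE rejected 8.6%, 12.1% and 15.8% of the time without the count at k = 0.2, 0.4 and 0.8, and 7.7%, 9.3% and 10.2% with it. The sandwich variance gave 5.2 to 6.1% throughout. The covariate therefore needs to come with a variance that allows overdispersion.

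**Limits.** The k values are assumptions. The simulated models omit the stratification factors and assume that prior events are counted without error at the same underlying rate as the outcome. If the strata already capture part of the risk, or history is recalled poorly, the gain is smaller.

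**The case against.** The strongest case against is that this is a preference. A stratification-adjusted Poisson comparison is an accepted primary analysis for a randomised trial, and a condensed article may leave a fuller covariate list to an analysis plan that is not shown. The sample size assumes Poisson counts and the pilot variance is below Poisson, so on the plan's own figures the covariate gains nothing. All of that stands, and it is why the point is limited to efficiency. The pilot is nevertheless weak evidence of uniform risk. It covers bronchiectasis in one city and events needing hospital clinic attendance or admission, whereas the trial counts symptom-defined episodes across three diagnoses and three cities.

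Several stronger readings are tempting but unsupported:

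- **That the count is already on file and free to use.** Only the threshold of two or more is documented.
- **That covariates will be chosen after the fact, or by baseline P-values.** The modelling is announced in advance under secondary analyses, and nothing links the baseline tests to covariate selection or says that the reported efficacy would be replaced.
- **That baseline tests breach the reporting standard the article cites.** The documents do not reproduce that standard's content. The argument against the tests rests on randomisation alone.
- **That the primary analysis is invalid or clearly underpowered without the covariate.** Neither follows.

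**Conclusion.** The point holds as a modest efficiency improvement. The stated adjustment covers site, age and aetiology and leaves out prior exacerbation frequency, a plausible predictor that must be assessed at entry. Under pure Poisson counts, adding it neither helps nor does material harm. Under an assumed frailty variance of 0.2 to 0.8, it lowers the variance of the log rate ratio by very roughly 5 to 20% and adds about 2 to 9 points of power for a 30% reduction, provided the variance estimator allows overdispersion. The documents give no figure for between-child heterogeneity, so the size is conditional. The baseline tests and the open-ended confounder modelling are minor wording points that do not change the primary estimate as planned.

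**What to change.** - Prespecify the primary model as arm + stratification factors + log of the exacerbation count in the 18 months before entry, with a log person-time offset and a sandwich or quasi-Poisson variance. Criterion 7 guarantees a count of at least two, so the log is always defined.
- Record the exact count on the baseline form if only the threshold is captured, and recover it for children already enrolled. This is the only real cost.
- Delete the between-arm tests of baseline characteristics and keep the descriptive summaries.
- State that the univariate and multivariate analyses are exploratory and do not alter the reported vaccine efficacy.

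The rest is wording. Recruitment began in January 2013, the article appeared in September 2013, and each child needs 14 months from enrolment, so at publication no child could have completed primary follow-up and the model could still be fixed before outcomes were known.

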#### Secondary analyses

The proportion of children with nasopharyngeal carriage of *H. influenzae* and *S. pneumoniae* at each time point will be compared between vaccine groups and presented as RR and 95% CI, adjusted for repeated measures. VE (%) against carriage will be calculated as (1-RR)*100 and presented with its 95% CI. Bacterial load at each time point will be compared.

Serum and mucosal antibody responses to *H. influenzae* proteins, including PD, pneumococcal protein and polysaccharide antigens and opsonophagocytic killing assays: geometric mean titres at each sampling time point will be compared between groups presented as a mean difference (and 95% CI) from linear regression models. In addition, the proportion of children assessed to be seropositive will be compared between groups at each sampling time point using χ^2^ tests for proportions and logistic regression models to adjust for stratification. All differences will be presented with their 95% CIs.

Safety and reactogenicity of vaccination: descriptive analyses will be performed on the number, type and severity of local and systemic reactions and SAEs that occur following vaccination and presented by treatment group. Comparisons between groups will be performed using Student’s *t*-test for continuous variables and χ^2^ tests for proportions.

Sub-group analyses will be performed for all primary and secondary objectives to examine potential differences by study specific strata. Univariate and multivariate analyses will be performed to evaluate variables independently associated with study endpoints and to assess potential confounding factors in the association between vaccination and disease.

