There is a direct relationship between lower airway bacterial load and systemic and lower airway inflammation, risk of acute respiratory exacerbations and quality of life measures in adults with bronchiectasis [13]. *Haemophilus influenzae* (usually unencapsulated or non-typeable (NTHi) strains) is consistently the predominant pathogen found in the sputum of adults with bronchiectasis [14] and chronic obstructive pulmonary disease (COPD) [15-17]. It is also the most common bacterial pathogen isolated from the lower airways of children with PBB, CSLD or bronchiectasis, followed less often by *Streptococcus pneumoniae (pneumococcus)* and *Moraxella catarrhalis*[18,19]. Furthermore, acquiring new *H. influenzae* strains can lead to exacerbations in adults with COPD [15,20,21]. Acute exacerbations are also important in bronchiectasis as they are associated with lower quality of life (QoL) scores [22,23] and poorer long-term outcomes. In adults with bronchiectasis, the frequency of exacerbations, increased systemic inflammatory markers and *Pseudomonas aeruginosa* infection are each determinants of an accelerated pulmonary decline [24]. Amongst other factors, an increased mortality risk is associated with the degree of lung function impairment [25]. In children with bronchiectasis, no prospective study exists, but the only significant predictor of pulmonary decline found in one retrospective study was the frequency of hospitalised exacerbations [26].

While pneumococcal polysaccharide and protein conjugate vaccines seem to have had little impact on the incidence of these chronic pulmonary diseases [8,27], interventions targeting *H. influenzae* may be more successful in reducing exacerbations and leading to improved clinical outcomes. Indeed, adult studies provide “proof of concept” that a *H. influenzae* vaccine may be beneficial. A systematic review of six randomised controlled trials (RCT; 440 patients) reported oral monobacterial whole-cell, killed *H. influenzae* vaccine reduced the incidence of “bronchitis” episodes at three months (rate ratio 0.69; 95% confidence interval (CI) 0.41, 1.14) and six months after vaccination (rate ratio 0.82; 95% CI 0.62, 1.09) [28].

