### Specimen collection

All children will have nasopharyngeal swabs, saliva and serum collected at enrolment and at 2 months post-vaccine dose 1, and then at 1, 6 and 12 months following the second study vaccine dose (Figure 1). Nasopharyngeal specimens will be obtained with flocked swabs following World Health Organization (WHO) Guidelines [36] and placed in 1.0 ml of skim-milk-tryptone-glucose-glycerol broth. Saliva will be collected using large cotton-tipped swabs, which when soaked are put in a 15 ml tube and placed immediately on ice, while serum will be separated into multiple aliquots. All three specimen types from each child will be stored at local laboratories at −80°C before being transported frozen to the research laboratories.

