### Laboratory methods

#### Nasopharyngeal swabs

Batches of swabs will be thawed and 10 μL aliquots cultured overnight on selective media at 37°C in 5% CO_2_. *H. influenzae* and *S. pneumoniae* will be confirmed by standard techniques and routine susceptibility testing performed using the calibrated dichotomous susceptibility disc diffusion method [37]. Diversity of *H. influenzae* isolates will be determined by polymerase chain reaction (PCR)-ribotyping, while the Quellung method (antisera from Statens Serum Institute, Copenhagen, Denmark) will be used to serotype pneumococcal isolates [38].

Real-time quantitative PCR assays will be used to estimate *H. influenzae* and *S. pneumoniae* loads in nasopharyngeal specimens using an in-house multiplex assay. The *H. influenzae* target is *hpd*[39], which also helps differentiate between *H. influenzae* and the commensal *H. haemolyticus,* while the target for *S. pneumoniae* is *lyt*A [40]. Quantitative standards will be generated from the reference strains *S. pneumoniae* (ATCC 49619) and *H. influenzae* (ATCC 19418) obtained from the American Type Culture Collection.

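### The planned vaccine efficacy against H. influenzae carriage is a valid comparison of point prevalence but does not measure efficacy against acquisition, and the stated comparisons leave the enrolment swab and the ribotypes unused

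*Protocol article*

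**What the plan says.** The secondary objective and the secondary laboratory outcomes name nasopharyngeal carriage and load of *H. influenzae*. Acquisition is not named in either.

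The Secondary analyses section fixes the method: "The proportion of children with nasopharyngeal carriage of *H. influenzae* and *S. pneumoniae* at each time point will be compared between vaccine groups". The result is a relative risk (RR) adjusted for repeated measures, and "VE (%) against carriage will be calculated as (1-RR)*100". Bacterial load is to be compared at each time point, with no covariate named. The Analysis section adds: "All analyses will be performed on an intention-to-treat basis and will account for baseline stratification". The strata are site, age group and diagnosis (Randomisation, allocation and blinding).

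Two further sources of data are planned. Specimen collection states: "All children will have nasopharyngeal swabs, saliva and serum collected at enrolment and at 2 months post-vaccine dose 1", with later swabs 1, 6 and 12 months after dose 2, that is, at about 3, 8 and 14 months. The section on nasopharyngeal swabs states: "Diversity of *H. influenzae* isolates will be determined by polymerase chain reaction (PCR)-ribotyping", and plans quantitative PCR for load. Neither enrolment carriage, enrolment load nor ribotype appears in the stated carriage and load comparisons.

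**The concern.** Point prevalence cannot tell a persistent carrier from a child who cleared one strain and gained another. If the vaccine prevents new strains from establishing but does not clear old ones, part of its effect is invisible in the proportion positive.

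The article itself treats acquisition as relevant:

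- The Background says that "acquiring new *H. influenzae* strains can lead to exacerbations in adults with COPD".
- It cites a Dutch infant trial that reported VE on colonisation (0.5%) and on acquisition (10.9%) separately.
- The closing paragraph of the Discussion lists acquisition of new strains among the questions of interest, and says that clinical efficacy will be read alongside carriage.

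A near-null VE on prevalence could therefore be taken as no effect on *H. influenzae* when acquisition had fallen. Separately, leaving out the enrolment value gives up precision and leaves chance imbalance in enrolment carriage uncorrected.

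**Working it through.** **Stated figures.** The article gives no prevalence, target VE or power for carriage. Its sample size concerns exacerbations only. With 93 per group and rates of 2.1 and 1.47, power is Φ(|ln 0.7| / √(1/(93×2.1) + 1/(93×1.47)) − 1.96) = Φ(1.24) = 89%, against 90% stated. Only the 93 per group is carried forward.

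**Model (assumed).** Children move between carrying and not carrying, with acquisition rate λ and clearance rate μ. Control prevalence is p = λ/(λ+μ). From dose 1 the vaccine multiplies λ by (1−v) and leaves μ unchanged. I take v = 30%.

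**Settled loss.** Vaccine-arm prevalence is p(1−v)/(1−pv), so VE on prevalence = v(1−p)/(1−pv).

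| p | VE on prevalence | Share of effect lost |
|---|---|---|
| 5% | 28.9% | 4% |
| 20% | 25.5% | 15% |
| 38.9% | 20.8% | 31% |
| 50% | 17.6% | 41% |
| 60% | 14.6% | 51% |
| 70% | 11.4% | 62% |

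The article's own figures for other populations are about 5% (Latin American infants) and up to 38.9% (healthy Czech controls). The loss also depends on v: at 60% prevalence and v = 50%, the share kept is 0.4/0.7 = 57%, so 43% is lost.

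**By visit.** Vaccine-arm prevalence at t months is q + (p−q)·exp(−(λ(1−v)+μ)t), where q is its settled value. VE on prevalence at p = 40%:

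| Mean carriage | 2 mo | 3 mo | 8 mo | 14 mo |
|---|---|---|---|---|
| 3 months, all children | 12.8% | 15.7% | 20.0% | 20.4% |
| 3 months, negative at enrolment | 26.0% | 24.6% | 21.1% | 20.5% |
| 6 months, all children | 7.9% | 10.6% | 17.6% | 19.8% |

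The early loss occurs even at low prevalence: at p = 5% with 3-month carriage, VE at 2 months is 14.4%. By 14 months, dropping enrolment carriers changes almost nothing (20.5% against 20.4%).

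**New ribotype in all children.** Assume each acquisition is a new ribotype and carriers do not gain a second strain. The proportion with a new ribotype at a visit is then P(t) − P(s)·exp(−μ(t−s)), where s is the previous swab and P is prevalence. For p = 40% and 3-month carriage:

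| Visit | Control | Vaccine | VE |
|---|---|---|---|
| 2 mo | 19.5% | 14.4% | 26% |
| 3 mo | 11.3% | 8.7% | 23% |
| 8 mo | 32.4% | 25.6% | 21% |
| 14 mo | 34.6% | 27.5% | 20.5% |

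Pooled over visits, new-ribotype VE is 22% against 17% on prevalence. With p from 20% to 60% and carriage of 3 or 6 months, the pooled ranges are 17–27% and 11–20%. The new-ribotype figure is nearer the true 30% in each case but still below it.

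**Power.** For the same case with 93 per arm, prevalence gives 14% at 3 months and 21% at 14 months. The new-ribotype outcome at 14 months gives Φ(0.0709/√((0.3459×0.6541 + 0.2750×0.7250)/93) − 1.96) = Φ(−0.91) = 18%; the same formula gives about 9% at 3 months. The gain is in what is estimated, not in the test.

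**Covariate.** Suppose half carry at enrolment, and later positivity is 60% in those children and 30% in the rest (assumed). Total variance is 0.45×0.55 = 0.2475. Within enrolment status it is 0.5×0.24 + 0.5×0.21 = 0.225, about 9% less.

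**The case against.** The case for leaving the plan alone is strong in several respects. The analysis matches its objective and outcome, is correctly labelled as efficacy against carriage, and compares randomised groups. The Background opens its argument with bacterial load, which is an outcome here, and the sentence on acquiring strains concerns adults with chronic obstructive pulmonary disease. The Discussion says that lavage would answer strain questions best and is not ethically possible. It also already warns that carriage and disease may diverge. The Dutch intervals (−21.8% to 18.4% and −31.3% to 38.9%) overlap widely, so that trial shows reporting practice and not a proven difference. The full protocol and the SAP are not shown and may contain an acquisition analysis.

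Most of this stands. There is no contradiction and no invalid test. It does not remove the two improvements, because the article does state its method and its adjustments, and these do not use the enrolment value or the ribotypes. That lavage would be better is no reason to leave planned nasopharyngeal typing out of the estimate.

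A reader might infer three stronger things that the documents do not support:

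- **That the effect is heavily diluted.** No carriage rate for these children is given, and the settled loss runs from about 4% to more than half.
- **That children already carrying at enrolment are the cause throughout.** They matter at the early visits. By 14 months the loss comes almost wholly from turnover of carriage.
- **That power is much better among children negative at enrolment.** That is a different outcome from new ribotypes in all children and does not bear on the proposal.

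**Conclusion.** The planned VE against carriage is valid for point prevalence and should stay. It is not VE against acquisition, and it understates an acquisition-only effect. For a true 30% effect, the settled loss is about 4% at 5% prevalence and just over half at 60%. The loss is largest at the 2- and 3-month visits, more so when carriage is long. These sizes assume a two-state model, a vaccine effect complete from dose 1, unchanged clearance, and prevalence and duration that the article does not give.

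Leaving out the enrolment value costs precision, about 9% of the variance under the assumed 60% and 30%. The point concerns one group of secondary outcomes. The primary outcome is unaffected.

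**What to change.** In the Secondary analyses section:

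1. Enter enrolment carriage status as a covariate in the prevalence comparison, and enrolment log load in the load comparison, alongside the stratification factors. This gains precision and guards against chance imbalance at enrolment.
2. Keep VE on prevalence as planned. Add a supplementary RR and VE, in all randomised children, for an *H. influenzae* ribotype not found on any earlier swab from that child, over the post-vaccination visits and with the same repeated-measures adjustment. Children with no isolate count as having no new ribotype, so the randomised comparison is kept.
3. State that VE on prevalence is not to be read as VE against acquisition.

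The cost is wording and analysis time, since the swabs, load assays and typing are already planned. There are two small downsides. Strains gained and cleared between widely spaced swabs are missed, and power for carriage effects remains low, so both results should be reported as estimates with intervals.

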#### Secondary laboratory outcomes

Nasopharyngeal carriage and load of *H. influenzae* and *S. pneumoniae* and *s*ystemic and mucosal immunity to *H. influenzae* proteins (PD, P4, P6) and PHiD-CV pneumococcal vaccine-type and vaccine-related serotypes at 2 months post-dose 1, and then at 1, 6 and 12 months following the second vaccine dose.

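### Geometric mean titres should be compared as a ratio, from a log-titre model that includes the enrolment titre, and not as a mean difference

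*Protocol article*

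**What the plan says.** The comparison of serum and mucosal antibodies and of the opsonophagocytic assays is set out in one sentence of the protocol article, under Secondary analyses: "geometric mean titres at each sampling time point will be compared between groups presented as a mean difference (and 95% CI"), taken from linear regression. The sentence names no transformation, no back-transformation and no covariates.

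On sampling, Specimen collection says: "All children will have nasopharyngeal swabs, saliva and serum collected at enrolment and at 2 months post-vaccine dose 1", with three later visits. Secondary laboratory outcomes places the immune endpoints "at 2 months post-dose 1, and then at 1, 6 and 12 months following the second vaccine dose". A pre-vaccination value is therefore planned for each child, alongside four post-vaccination values.

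On adjustment, the Analysis section says: "All analyses will be performed on an intention-to-treat basis and will account for baseline stratification". Secondary analyses later adds a general statement: "Univariate and multivariate analyses will be performed to evaluate variables independently associated with study endpoints". It lists no variables, and neither statement mentions the enrolment titre.

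**The concern.** A geometric mean is the antilog of a mean of logs. Two of them are compared by dividing one by the other. A mean difference is the contrast for arithmetic means, or for logs before back-transformation. The sentence pairs one kind of summary with the other kind of contrast, and the reader cannot tell what unit the reported number will have. The same section does name a ratio where one is meant: carriage is to be reported as a relative risk.

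The second part concerns precision. Children enter between 18 months and 14 years of age with different histories of vaccination and carriage, so pre-vaccination titres can be expected to vary. The stratification factors take up some of that variation, since age below or above six years is one of them. The child's own enrolment titre would usually take up more.

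The immune response is the second of the secondary objectives, and the Discussion says clinical efficacy will be read alongside immunogenicity. An effect measure of unclear scale, with intervals wider than they need be, makes that reading harder.

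**Working it through.** **No figure to reproduce.** The article gives no power, standard deviation or baseline correlation for the antibody outcomes. Everything numerical below rests on stated assumptions. The group size of 93 is the evaluable number from Sample size ("93 children per group will provide 90% power (α = 0.05, two-sided"), which was set for the primary endpoint and is used here only for scale.

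**Step 1: what a linear regression of log titre estimates.**

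mean(log titre, PHiD-CV) − mean(log titre, control) = log(GMT, PHiD-CV) − log(GMT, control) = log(GMT ratio)

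The coefficient is a difference in logs. It becomes a comparison of geometric means once it is back-transformed. For an assumed GMT ratio of 1.5, the coefficient on log10 titre is log10(1.5) = 0.176, and 10^0.176 = 1.5. A reported mean difference of 0.176 would have no meaning in titre units; the ratio of 1.5 would.

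**Step 2: gain from the enrolment titre.** Let ρ be the correlation between enrolment and follow-up log titre within vaccine group, after the stratification factors.

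Residual variance with adjustment = (1 − ρ²) × unadjusted variance

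CI width factor on the log scale = √(1 − ρ²)

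Equivalent number per group = 93 / (1 − ρ²)

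| Assumed ρ | 1 − ρ² | CI width factor | Equivalent n per group |
|---|---|---|---|
| 0.3 | 0.91 | 0.95 | 102 |
| 0.5 | 0.75 | 0.87 | 124 |
| 0.7 | 0.51 | 0.71 | 182 |

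**Step 3: the same gain on the ratio scale.** With an assumed log10 SD of 0.5 and 93 per group, the half-width of the 95% CI in log10 units is 1.96 × 0.5 × √(2/93) = 0.144 without adjustment. The interval for the GMT ratio is then the estimate multiplied and divided by 10^0.144 = 1.39. With ρ = 0.5 the half-width is 0.144 × 0.866 = 0.124 and the factor is 1.33. With ρ = 0.7 it is 0.144 × 0.714 = 0.103 and the factor is 1.27.

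**Step 4: bias.** The enrolment sample precedes vaccination and allocation is random, so its distribution is the same in both groups in expectation. Leaving it out does not bias the group comparison, and neither does putting it in. Only precision changes.

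**The case against.** The strongest reply is that the plan is probably right and only loosely worded. Linear regression compares geometric means only when the outcome is log titre, so the natural reading is a log-scale model whose coefficient is called a mean difference. On that reading the method agrees with the fix in Step 1 except for the back-transformation. This stands. It limits the first part to a mismatch between the summary and the stated effect measure.

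A reader might go further and infer that raw titres will be regressed, so that arithmetic means are compared on the wrong scale. The documents do not support that: no section says titres are modelled untransformed. The inference would matter if it were true. In a simulation with 93 per group, an assumed GMT ratio of 1.5 and a log10 SD of 0.5, power was 67% on log titres and 43% on raw titres. That is a reason to state the scale. It does not show that the plan has chosen the wrong one.

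The second reply is that a condensed article commonly leaves covariates to the analysis plan, and that the enrolment titre is nowhere excluded. The general statement on multivariate analyses could cover it, and the comparison at each sampling time could include enrolment. This also stands. It cannot be said that the plan leaves out the enrolment titre or wastes the baseline sample. What can be said is that the one adjustment fixed for all analyses is stratification, and that a better covariate is to hand.

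The third reply is that the gain may be small. At ρ = 0.3 the interval narrows by only about 5%. That is fair, and the lower end belongs in the range.

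**Conclusion.** The point holds in a limited form. The stated effect measure, a mean difference, does not fit the geometric means it is meant to compare; the matching contrast is a ratio, and the article gives no scale from which a reader could recover it. This follows from the text alone and needs no assumption.

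Adding the enrolment titre is a recommended improvement, not the correction of an error. It would shorten the confidence intervals by about 5%, 13% or 29% on the log scale for assumed correlations of 0.3, 0.5 or 0.7. Those figures depend on correlations that the article does not give, and on ρ being what remains after the stratification factors have been taken into account. No bias is at issue.

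The matter is confined to the secondary immunogenicity outcomes. The primary comparison of exacerbation incidence is not touched.

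**What to change.** Replace the mean difference with the following. At each post-vaccination visit, log titre (and log opsonisation index) is regressed on vaccine group, log enrolment titre and the stratification factors. The group coefficient is back-transformed and reported as the geometric mean ratio, PHiD-CV over control, with its 95% confidence interval.

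One detail should be settled with it. Serum samples says the opsonophagocytic assay is run only on serum from children with no antibiotics in the three days before venesection, so some children will lack an enrolment value for that assay. State how a missing enrolment value is handled, so that no child with a follow-up value is dropped and the intention-to-treat statement holds.

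The cost is wording in the protocol and the analysis plan. The enrolment specimens are already part of the schedule. The article does not say whether they have been assayed, but a comparison at each sampling time suggests that they will be. The change should be made before the randomisation code is broken, so that neither the scale nor the covariate can be chosen in the light of the results.
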